#### Patient Health Questionnaire-4

The German version of the Patient Health Questionnaire-4 (PHQ-4)^40^ assesses anxiety and depression using four items on a 4-point Likert scale (0=‘not at all’; 3=‘almost every day’). The values are added for the total score, higher values indicating a greater extent of anxiety and depression. The scale showed good internal consistency with α>0.80. A factor analysis revealed a good fit with 84% of the total variance explained. In a recent study, the internal consistency of the instrument for the German population could be again confirmed as good (ω=0.85).^41^

#### Fear of Progression Questionnaire Short Form

The Fear of Progression Questionnaire Short Form (PA-F-KF)^42^ consists of 12 items that are answered on a 5-point Likert scale (1=‘never’; 5=‘very often’). The questionnaire assesses the patient’s fear of progression on five dimensions (affective reaction, partnership/family, occupation, loss of autonomy) and shows overall good internal consistency (α=0.87).^42^ The construct validity of the items was confirmed by correlating the items to other measures assessing similar constructs (Hospital Anxiety and Depression Scale, HADS; Posttraumatic Stress Disorder Checklist - Civilian Version, PCL-C; Short Form-8 Health Survey, SF-8; Life Attitude Profile – Revised, LAP-R). A factor analysis revealed a one-dimensional structure, explaining 42% of the total variance.^42^ The psychometric properties were also confirmed in more recent studies. For example, a study by Hahn^43^ found an internal consistency of α=0.88 for the PA-F-KF.

#### Minimal Documentation System version 2

The Minimal Documentation System (MIDOS-2)^44^ is a self-report questionnaire assessing participants’ symptom-related afflictions due to chemotherapy-associated side effects on a 4-point Likert scale (0=‘none’; 3=‘major afflictions’). In total, there are 13 items. Ten items are measuring the side effects pain, nausea, regurgitation, shortness of breath, constipation, weakness, lack of appetite, fatigue, depression and anxiety. Two more items leave open spaces for naming other afflictions and one more item assesses how the participant is feeling that day, ranging from 0 (‘very bad’) to 4 (‘very good’). The sum score of each item describes the extent of complaints for each participant. The questionnaire reveals good psychometric properties, with internal consistencies varying between α=0.67 and 0.73 and the test-retest variability varying between r=0.69 and r=0.57.^44^ The psychometric properties were also confirmed for patient groups in non-palliative care.^45^

#### Heart rate and blood pressure

Heart rate and blood pressure are measured continuously from the beginning to the end of the intervention in 5-minute intervals in bpm using a pulse oximeter and blood pressure monitor. A member of the study team records these values while accompanying the intervention.

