**Trial registration number:**

German Clinical Trials Register (DRKS00029738).

STRENGTHS AND LIMITATIONS OF THIS STUDYRandomised controlled trial that compares the effectiveness of two interventions (virtual reality mindfulness and music) to a control group.Assessment of a clinical population undergoing active oncological treatment.In addition to psychological assessments and self-ratings, saliva samples used to measure cortisol levels, heart rate and blood pressure are evaluated and provide a more objective method.Limited standardisation of the assessment environment, making it challenging to control for potential confounding variables during data collection.

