#### Music intervention

The receptive music intervention is delivered via an MP3-player (Apple iPod)^29^ and circumaural headphones (Bose Corporation).^27^ Prior to the first intervention, the participants can choose between four genres (classic, jazz, meditation and lounge) and will listen to this genre at both intervention time points. The playlists consist of music titles selected by a music psychologist according to the recommendations of Nilsson^30^ and used in a previous project of our group.^31^ They can be accessed in online supplemental appendix B. All tracks are instrumental and vary between 60 and 80 beats per minute (bpm). The music intervention lasts 15–20 min. Table 1 presents a comparative overview of the VR and the music intervention.

**Table 1 T1:** Comparative overview of the virtual reality and the music intervention

Intervention design feature	VR intervention	Music intervention
Intervention type	Active	Receptive
Delivery format	Immersive VR environment via head-mounted display with headphones	Music via MP3 player and headphones
Technology	Quest 2 (Meta), Bose headphones	Apple iPod, Bose headphones
Intervention content	Mindfulness exercise, environment meditation in a natural environment with nature sounds	Listening to instrumental music (60–80 bpm)
Degree of user choice	Predefined meditation without choice options	Choice of four different music genres: classic, jazz, meditation or lounge
Type of guidance	Verbal guidance by a male narrator (directing attention to various aspects of the environment)	No guidance
Duration	15 min (+up to 5 min for acclimatisation)	15–20 min

bpm, beats per minute; VR, virtual reality.

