### Measures

Patients complete four different types of questionnaires during their study participation at the following measurement time points: after recruitment (T0; baseline), before the intervention (preintervention), after the intervention (postintervention) and at the end of the study (evaluation). All questionnaires were used in the German version. Additionally, physiological parameters (heart rate and blood pressure) are measured during the intervention phase. The preintervention, during-intervention and postintervention measurements are administered two times over two consecutive chemotherapy sessions (T1 and T2). Table 2 outlines the measures employed and the corresponding time points at which they are collected. Furthermore, saliva samples are collected both before and 25 min after the intervention, while heart rate and blood pressure are recorded at 5-minute intervals during the intervention. A detailed presentation of all measures used in the study is described in the following sections.

**Table 2 T2:** Overview of measures used for the study and the measurement time points

Measure	Baseline	Preintervention	During intervention	Postintervention	Evaluation
Demographic data	X				
Cancer-related data	X				
VAS-social support	X				
Previous experiences with mindfulness and music for relaxation	X				
ASKU	X				
PHQ-4	X	X			
STAI-trait	X				
Salivary cortisol		X		X	
STAI-state		X		X	
PA-F-KF		X		X	
MIDOS-2		X		X	
VAS-anxiety		X		X	
VAS-relaxation		X		X	
Heart rate			X		
Blood pressure			X		
VAS-tolerability of chemotherapy				X	
VAS-perceived duration of chemotherapy				X	
PSSUQ*					X
VR-specific evaluation (self-developed)*					X
Music-specific evaluation (self-developed)†					X

* VR group only

† Music group only

ASKU, Short Scale for Measuring General Self-efficacy Beliefs; MIDOS-2, Minimal Documentation System version 2; PA-F-KF, Fear of Progression Questionnaire Short Form; PHQ-4, Patient Health Questionnaire-4; PSSUQ, Post-study System Usability Questionnaire; STAI, State-Trait Anxiety Inventory; VAS, Visual Analogue Scale; VR, virtual reality.

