**Figure 2 F2:**
[figure not shown]
Participant timeline. VR, virtual reality.

The study team screens for general anxiety symptoms using the GAD-7 questionnaire.^20 21^ To ensure that participants are experiencing a level of anxiety significant enough to benefit from the interventions and demonstrate measurable changes in the primary outcome variable, only patients with at least moderate anxiety (defined as a score ≥5) are included in the study. Patients are randomly assigned to one of three intervention arms using computer-generated random numbers; however, they remain blinded to their group allocation until the first intervention time point (T1).

After recruitment, participants complete the first questionnaire for baseline assessment (T0). The intervention begins during the subsequent chemotherapy session at the IAC (T1). At this point, patients are informed of their study allocation and receive the preintervention questionnaire. Following the completion of the questionnaires, and after the flushing and premedication processes as part of the chemotherapy session, patients provide the first saliva sample by insalivating a cotton swab. The study team then assists patients in initiating the intervention.

Patients in intervention group 1 wear a VR headset and headphones and begin the mindfulness exercise. Patients in intervention group 2 put on headphones and listen to music. Patients in the control group 3 receive no additional treatment. A member of the study team remains with the patient, collecting data on heart rate and blood pressure at 5-minute intervals. After approximately 15–20 min, the intervention concludes. Patients then complete the postintervention questionnaire, and a second saliva sample is collected after 25 min. This procedure is repeated during the subsequent chemotherapy session (T2). Finally, patients in all groups receive a questionnaire specifically evaluating the intervention immediately after the second measurement time point. Participants in groups 2 and 3 are given the opportunity to try the VR intervention independently of data collection.

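### Heart rate and blood pressure have no scheduled pre-intervention reading, and the timing of the first reading relative to fitting the headset or headphones is left open

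*Protocol article*

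**What the plan says.** Every place in the protocol article that times heart rate and blood pressure puts them inside the intervention.

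- **Heart rate and blood pressure** (secondary outcome measures): "Heart rate and blood pressure are measured continuously from the beginning to the end of the intervention in 5-minute intervals".
- **Measures**: "heart rate and blood pressure are recorded at 5-minute intervals during the intervention". Table 2 marks both only in the during-intervention column.
- **Recruitment and participant timeline**: the pre-intervention questionnaire comes first, then flushing and premedication, then "patients provide the first saliva sample by insalivating a cotton swab. The study team then assists patients in initiating the intervention". Vital signs appear only after that: "A member of the study team remains with the patient, collecting data on heart rate and blood pressure at 5-minute intervals". The session is short: "After approximately 15–20 min, the intervention concludes".

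Cortisol is handled differently (Measures): "saliva samples are collected both before and 25 min after the intervention". Table 2 also gives STAI-state, PA-F-KF, MIDOS-2, VAS-anxiety and VAS-relaxation both a pre and a post value.

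The strengths and limitations box groups the three physiological measures and presents them as a strength: "saliva samples used to measure cortisol levels, heart rate and blood pressure are evaluated and provide a more objective method".

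For the VR arm, Table 1 gives the duration as "15 min (+up to 5 min for acclimatisation"). For music it gives 15 to 20 min with no acclimatisation phase.

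**The concern.** An acute effect on a physiological variable is normally read against a value taken just before exposure. Here no such value is scheduled, and no later analysis can recover a reading that was not taken. Three things follow.

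1. The before/after factor that the Statistical analysis section uses for STAI-state has no counterpart for heart rate and blood pressure.
2. If the first in-session reading is used as a baseline, it may not be neutral between arms. The VR headset is adjusted to the patient's head, and the Risk to patients section itself lists stress or anxiety from the technical set-up as a possible VR risk. If the first reading follows fitting, change from it could hide such a response or count recovery from it as relaxation.
3. The clock may not mean the same in each arm. The first VR interval may be acclimatisation while the music patient is already listening. The article names no event that starts the clock in the control arm.

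At stake is how precisely and how clearly two outcomes can be read that the article offers as more objective evidence.

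**Working it through.** **Step 1. Is a pre-device reading scheduled anywhere?** The outcome definition, the Measures text, Table 2 and the participant timeline agree: readings occur during the intervention. The steps listed before it are the questionnaire and the saliva sample. No pre-intervention reading is scheduled.

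**Step 2. When is the first reading?** The outcome definition starts at the beginning of the intervention, which can mean minute 0. The timeline mentions the readings only after staff have helped to start the intervention. Neither says whether the device is already on. The point is open.

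**Step 3. How many readings?** At 5-minute spacing over 15 to 20 min:

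- with minute 0 counted: 15/5 + 1 = 4 to 20/5 + 1 = 5;
- without it: 3 to 4.

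**Step 4. Number per arm, from the plan's own sample size.** Inputs from the Sample size section: effect size f = 0.25, α = 0.05, power 0.95, k = 3 groups, m = 2 time points, N = 66. The article gives no within-patient correlation, so ρ = 0.5 (the G*Power default) is assumed. For the within-between interaction:

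- λ = f²·N·m/(1 − ρ) = 0.0625 × 66 × 2 / 0.5 = 16.5;
- degrees of freedom: (k − 1)(m − 1) = 2 and (N − k)(m − 1) = 63;
- power = 0.9535, and 66 is the smallest multiple of 3 that reaches 0.95.

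The stated N is reproduced. Allowing for 20% dropout gives 66/0.80 = 82.5, against the stated 82. This calculation does not involve heart rate or blood pressure, so adding a reading changes neither figure. Equal allocation of 66 gives 22 per arm.

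**Step 5. Precision without and with a baseline.** For a pairwise comparison, two-sided α = 0.05 and 80% power, in SD units of the in-session outcome:

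- no baseline: (1.960 + 0.842) × √(2/22) = 2.802 × 0.3015 = 0.845;
- adjusted for a baseline with correlation r: 0.845 × √(1 − r²).

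| Assumed r | 1 − r² | Detectable difference (SD) | Sample-size factor 1/(1 − r²) |
|---|---|---|---|
| none | 1 | 0.85 | 1 |
| 0.3 | 0.91 | 0.81 | 1.10 |
| 0.5 | 0.75 | 0.73 | 1.33 |
| 0.7 | 0.51 | 0.60 | 1.96 |
| 0.8 | 0.36 | 0.51 | 2.78 |

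The correlations are assumptions; the article gives none. The comparator is an analysis with no baseline at all. If a minute-0 reading exists and is used as a covariate, the added gain from an earlier reading is smaller. Its size depends on correlations that the article does not give.

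**Step 6. Validity without a baseline.** In 20,000 simulated trials with 22 per arm and no true difference, a one-way comparison of in-session values rejected in 5.0% at the 5% level. The test keeps its size.

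**The case against.** The strongest case on the other side has five parts.

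- **Cortisol has a pre and a post sample.** A reader might infer that the trial's objective outcomes as a group cannot show change. The documents do not support this. The gap concerns heart rate and blood pressure only. This stands.
- **Heart rate and blood pressure are still usable.** Three to five readings per session allow a comparison of within-session course, and randomised arms can be validly compared on level. A reader might call these outcomes close to uninformative; Steps 5 and 6 show a loss of precision, not of validity. This stands.
- **The first reading may be at minute 0, before the device.** That the intervention is already running at the first reading is an inference the text does not settle. The structured documentation form also records start and end times, which may help to align the clock afterwards. This stands in part: recorded times can align readings but cannot supply one that was not taken. The schedule itself is stated in Table 2, so it has not been left to a fuller document.
- **The proposed reading is not perfectly clean.** At T1 patients learn their allocation before the questionnaire and the saliva sample, so anticipation could already differ by arm. This stands, and it limits what the fix achieves. Such a reading would still precede the device.
- **The outcomes are exploratory.** The Statistical analysis section says so for all secondary criteria. This stands and bounds the importance of the point.

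**Conclusion.** The point holds in limited form. No pre-intervention heart-rate or blood-pressure reading is scheduled, and the position of the first reading relative to device fitting is undefined. Change from a true pre-device level cannot be estimated. Change from the first in-session reading may be contaminated by set-up in the VR arm, but only if that reading follows fitting, which the article leaves open.

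The cost is mainly precision: a detectable difference of about 0.85 SD without a baseline, against 0.73 SD at r = 0.5 or 0.60 SD at r = 0.7. This rests on 22 patients per arm, the assumed correlations and a comparator with no baseline. A reader might conclude from high correlations that several times as many patients are needed. That would depend on unsupported values of r and would ignore any minute-0 reading; at r = 0.5 the factor is 1.33.

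The primary outcome, which is measured before and after, and the sample size of 66 (82 with dropout) are unaffected. This is a cheap improvement to exploratory secondary outcomes, not a threat to the trial's main conclusion.

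**What to change.** For remaining patients:

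1. Take one heart-rate and blood-pressure reading at the first saliva sample, before headset or headphones are fitted and at the same point in the control arm. Mark it as pre-intervention in Table 2.
2. Start the 5-minute clock when the meditation, the music or the control observation starts, so that VR acclimatisation falls outside it.
3. Compare arms on the mean in-session reading (for example at 5, 10 and 15 min, which all arms can provide), adjusted for the pre reading.
4. For patients already measured, state when the first reading was taken relative to device fitting, and limit claims about change accordingly.

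The practical cost is one reading a few minutes earlier, with the monitor and staff member already present. The statistical cost is that patients measured under the present scheme lack the value and need an unadjusted or separate sensitivity analysis. If few patients remain, the gain shrinks and item 4 becomes the main remedy. Because allocation is disclosed first, the new reading precedes the device but not knowledge of the arm, and the report should say so.

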#### Saliva cortisol

Salivary samples are assessed to measure levels of cortisol in nmol/L. For this purpose, each participant insalivates a cotton swab for at least 30 s before the beginning of the intervention and 25 min after the end of the intervention. All saliva samples are stored in the dark at −20°C. Analyses will be carried out by Dresden LabService GmbH, Technical University of Dresden, Germany, using chemiluminescence immunoassay.

#### Evaluation

The evaluation was conducted for all three study arms, with tailored formats for each intervention group as well as the control group. For the VR group, seven items from the Post-Study System Usability Questionnaire^46^ (items 1, 6, 11, 16–19) were used. The full questionnaire consists of 21 items and was translated into German during a previous study conducted by our group.^47^ The selected items have been slightly adapted to better fit the specific VR application used in the study. Responses are given on a 7-point Likert scale (1=‘strongly disagree’; 7=‘strongly agree’), with the overall score reflecting the perceived usability of the VR system by the patients.

Additionally, patients were asked to rate several self-developed items that were tailored to the specific intervention (VR or music). These items assess whether the intervention was pleasing, relaxing, boring or annoying, whether it helped to alleviate any unpleasant feelings, induce calmness and create a pleasant atmosphere during the chemotherapy session. Patients also rated whether they liked the intervention, whether they would choose to use it again in a future chemotherapy session, whether they could focus more on the intervention than on their own thoughts, and whether they were already familiar with the intervention. All these items are also rated on a 7-point Likert scale (1=‘strongly disagree’ 7=‘strongly agree’).

Finally, all groups were asked to indicate which type of intervention (VR, music or none) they would prefer to use during a future chemotherapy session, rated on a 7-point Likert scale (1=‘not at all’; 7=‘very much’). The evaluation questionnaire also includes two additional free-text fields titled ‘Suggestions for enhancing the utilisation of VR/music’ and ‘Other comments’. The complete evaluation questionnaire is available for review in online supplemental appendix D.

### Recruitment and participant timeline

The study team initiates contact with patients during their outpatient visit to the IAC and inquires about their interest in participating in the study. Subsequently, the treating physicians are consulted to confirm the patients’ eligibility for the study, and their approval is sought once eligibility is confirmed. Patients are then contacted again by the study team during their next chemotherapy session. All patients provide written informed consent prior to their participation in the study. Figure 2 shows the participant timeline. The patient information and consent form can be found in online supplemental appendix E.

**Figure 2 F2:**
[figure not shown]
Participant timeline. VR, virtual reality.

The study team screens for general anxiety symptoms using the GAD-7 questionnaire.^20 21^ To ensure that participants are experiencing a level of anxiety significant enough to benefit from the interventions and demonstrate measurable changes in the primary outcome variable, only patients with at least moderate anxiety (defined as a score ≥5) are included in the study. Patients are randomly assigned to one of three intervention arms using computer-generated random numbers; however, they remain blinded to their group allocation until the first intervention time point (T1).

After recruitment, participants complete the first questionnaire for baseline assessment (T0). The intervention begins during the subsequent chemotherapy session at the IAC (T1). At this point, patients are informed of their study allocation and receive the preintervention questionnaire. Following the completion of the questionnaires, and after the flushing and premedication processes as part of the chemotherapy session, patients provide the first saliva sample by insalivating a cotton swab. The study team then assists patients in initiating the intervention.

Patients in intervention group 1 wear a VR headset and headphones and begin the mindfulness exercise. Patients in intervention group 2 put on headphones and listen to music. Patients in the control group 3 receive no additional treatment. A member of the study team remains with the patient, collecting data on heart rate and blood pressure at 5-minute intervals. After approximately 15–20 min, the intervention concludes. Patients then complete the postintervention questionnaire, and a second saliva sample is collected after 25 min. This procedure is repeated during the subsequent chemotherapy session (T2). Finally, patients in all groups receive a questionnaire specifically evaluating the intervention immediately after the second measurement time point. Participants in groups 2 and 3 are given the opportunity to try the VR intervention independently of data collection.

